### Secondary endpoints

These consist of:i)Mortality at 30 days and 12 months post-TAVIii)Major adverse cardiovascular or cerebrovascular event (MACCE) at 30 days and 12 monthsiii)Acute myocardial infarction (MI) at 30 days and 12 monthsiv)Stroke at 30 days and 12 monthsv)Repeat revascularization by either PCI or CABGvi)Hospitalization for heart failure at 30 days and 12 monthsvii)Procedural complications (ventricular fibrillation (VF) or ventricular tachycardia (VT) requiring cardioversionviii)Requirement of cardiopulmonary bypassix)Cardiopulmonary arrest requiring cardiopulmonary resuscitation (CPR) and/or assisted ventilatory supportx)Procedural successxi)Bleeding complicationsxii)Access site complicationsxiii)Cerebrovascular eventsxiv)Acute kidney injuryxv)Duration of hospital stayxvi)Quality of lifexvii)Anginal burdenxviii)6-minute walk test

The definitions are in accordance with the Valve Academic Research Consortium (VARC) guidelines and its update and are specified in Table 2
[33].

**Table 2 Tab2:** **Endpoint definitions**

End-point	Definition
**Mortality**	All-cause death
**Cardiovascular mortality**	All deaths unless otherwise clearly documented to be related to another cause (for example, trauma, cancer, suicide *etcetera*)
**Myocardial infarction (MI)**	Peri-procedural MI related to TAVI (≤72 h after the TAVI)
	Spontaneous MI (>72 h after TAVI)
	MI related to PCI (type 4a)
	MI related to PCI due to stent thrombosis (type 4b)
**Cerebrovascular event**	Stroke
	Transient ischemic attack
**Bleeding complication**	Life-threatening or disabling
	Major
	Minor
**Access site complication**	Major
	Minor
**Acute kidney injury** As per AKIN classification in VARC2 [34]	Stage 1
	Stage 2
	Stage 3
**Major adverse cardiac and cerebrovascular events (MACCE)**	Combined cardiovascular mortality, MI, stroke and further revascularization

TAVI, transcatheter aortic valve implantation; PCI, percutaneous coronary intervention, AKIN, acute kidney injury network; VARC2, Valve Academic Research Consortium second guidelines [34].

### Ethics

Ethics review was approved by United Kingdom National Research Ethics Committee (London Dulwich) (11/LO/1596).

### Randomization

Randomization will take place once the patient has provided written, informed consent. This will be performed via an online portal. Randomization of the treatment assignment is based on the block method using randomly varying block sizes and will be stratified by center. Once the patient is randomized s/he will be monitored for the duration of the follow-up irrespective of subsequent clinical management. The intended timeframe for PCI should be stated at randomization. After PCI the patient should receive dual anti-platelet therapy for 30 days - one of which can then stop if the patient receives a bare-metal stent (BMS). All PCI patients should undergo TAVI within the 2 weeks after this 30-day post-PCI time point. Any clinical events which occur in the test arm during this period will be attributed to the percutaneous revascularization on an intention-to-treat-basis. The flow diagram in Figure 1 illustrates the recruitment and study process.

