### Why do we need a randomized trial?

The data on coronary artery disease in TAVI and PCI in this context is certainly provocative, but there are several major limitations, given that the studies are all nonrandomized, registry-type with relatively small sample sizes.

The lack of data on pre-procedural revascularization has led to some variability between centers on the level of coronary interventions undertaken prior to implantation. A retrospective analysis by Masson *et al*. stratified TAVI patients according to myocardium at risk due to coronary artery disease, finding no difference in 30-day or 1-year mortality between the groups [4]. However the small group sizes involved would have required a mortality difference between even the two most extreme groups at 30 days of greater than one third to gain significance, limiting our use of this data. The access approach used was not included in their risk model, an important omission given the known differences in risk profiles between, for example, TF-TAVI and TA-TAVI cohorts. In the German TAVI registry, CAD was defined as previous revascularization (either PCI or CABG) OR a stenosis of ≥50% and was noted in 62% of 1,382 patients. These patients had a greater in-hospital mortality (10.0 versus 5.5%, *P* <0.01), required more frequent cardio-pulmonary resuscitation (7.8 versus 3.5%, *P* <0.01) and suffered greater 30-day mortality (log rank *P* = 0.041). But there were significant differences in the group demographics: more frequent peripheral vascular disease, lower left ventricular (LV) ejection fraction and higher logistic EuroScores in patients with CAD [23]. The Italian CoreValve registry noted that in patients with critical ostial disease, myocardial infarction (MI) within 12 months of TAVI was greater in those patients who were not revascularized prior to TAVI [24]. A recent meta-analysis of the effects of CAD upon outcome in the midterm showed no effect; but again, of seven included studies, five defined CAD as previous revascularization, and the remaining two used 50% stenosis severity [25].

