### Trial conduct

ACTIVATION will be conducted at up to 20 hospitals in Europe providing TAVI using the Edwards system. Trial administration and data management will be carried out by an independent clinical trial organization, the European Cardiovascular Research Center, Massy, France. The trial is registered at http://www.controlled-trials.com (ISRCTN75836930).

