### Statistical consideration

#### Sample size determination

No randomized trials have been performed of elective PCI versus no PCI in patients undergoing TAVI. In a recent nonrandomized registry, Masson *et al*. reported a 1-year mortality of 20% in 15 patients who underwent PCI prior to TAVI - similar to those who did not at 22.1% [4] - despite the presence of existing coronary disease having been shown to increase mortality in patients undergoing TAVI from 18.4 to 35.7% [5].

With the postulation that improved coronary perfusion may protect against some of the ischemic/hypotensive procedural complications of the TAVI procedure, an improvement in rate of mortality seems likely. PCI may lead to restenosis of the stent, requiring rehospitalization in 5% of patients over 12 months. The rate of rehospitalization with stable angina, acute coronary syndrome or ischemia-related heart failure requiring treatment, including possible PCI, is thought to be in the region of 15% in all patients with CAD. The feasibility assumptions for 12-month mortality are 30% in the control (TAVI only) arm and 20% in the test (TAVI + PCI) arm, with similar rates of hospitalization at 15% in both. Based on the above assumptions, we performed sample size simulations and the simulated results show that with a non-inferiority margin of 7.5% and a loss to follow up of 5%, the sample size of 310 patients will have at least 88.8% power to demonstrate non-inferiority of TAVR following PCI compared with TAVR without PIC in the primary endpoint.

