### Statistical analysis

For the primary endpoint analysis, cumulative event rate will be calculated using the Kaplan-Meier estimates, and the Greenwood standard errors for these estimates. A 95% one-sided upper confidence limit will be computed for the difference in the primary composite outcome of mortality of rehospitalization at 12 months between arms (Test - Control). The Test arm (PCI) will be judged not inferior to the Control arm (no PCI) if the upper confidence limit is less than 7.5% - the predetermined non-inferiority margin. This was chosen based upon expert opinion and precedent (PARTNER cohort A [29]). In addition to formal analysis of non-inferiority endpoints, the Kaplan-Meier curves will be presented and compared by log rank test by treatment group and hazard ratio and its 95% confidence interval will be calculated using Cox regression model. Also, the combination of the all cause mortality and time to first recurrent hospitalization will be analyzed using the unmatched win ratio approach [35].

For secondary time-to-event outcomes, event rates at 30 and 365 days will be calculated using the Kaplan-Meier method and compared by log rank test. Their hazard ratios will be estimated using Cox regression model. Outcomes with repeated measurements will be analyzed using generalized linear mixed models. Continuous variables will be summarized using number of observations, median (interquartile range) or mean (SD) depending on variable distributions, whereas categorical variables will be summarized by the number and percentage of events. Chi-square tests and Mann-Whitney methods will also be used for comparative purposes. All analyses will be performed both on intention to treat and as treated populations.

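### Randomization is stratified by center, but the primary and supportive analyses name no stratum or baseline covariate; the cost is a little precision, not validity

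*Protocol article*

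**What the plan says.** Under Randomization, the protocol article says: "Randomization of the treatment assignment is based on the block method using randomly varying block sizes and will be stratified by center". Center is the only stratification factor named. Under Trial conduct, "ACTIVATION will be conducted at up to 20 hospitals in Europe", so 310 patients average about 15 per center (310 / 20 = 15.5).

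Under Statistical analysis, for the primary endpoint, "cumulative event rate will be calculated using the Kaplan-Meier estimates, and the Greenwood standard errors for these estimates", and "A 95% one-sided upper confidence limit will be computed for the difference in the primary composite outcome". Non-inferiority is declared if that limit lies below 7.5%. As support, the Kaplan-Meier curves are to be "compared by log rank test by treatment group and hazard ratio and its 95% confidence interval will be calculated using Cox regression model". Neither center nor any baseline covariate appears in these sentences.

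**The concern.** When randomization is blocked within centers and centers differ in prognosis, the arms are balanced on center by design, and the treatment difference varies less from trial to trial than under simple randomization. A Greenwood standard error computed on each whole arm does not credit that balance. It is therefore somewhat too large when center is prognostic, and the upper limit sits a little too high. An analysis that follows the randomization strata, and uses baseline factors related to outcome, can recover some of this.

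What is at stake is precision in a trial with a tight margin. At the planning rates the one-sided half-width is about 9.2 points against a margin of 7.5, so the test arm must look better than control before it can be declared non-inferior. Precision that costs almost nothing to obtain is worth having.

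**Working it through.** **Inputs.** From Sample size determination: 12-month mortality 30% (control) and 20% (test), hospitalization 15% in both arms, 310 patients, stated power at least 88.8%, and "with a non-inferiority margin of 7.5% and a loss to follow up of 5"%. From Statistical analysis: one-sided 95% limit. Assumed here: 1:1 allocation, and independence of death and hospitalization.

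**Step 1: reproduce the stated power.**
- Composite rates: control 1 - 0.70 × 0.85 = 40.5%; test 1 - 0.80 × 0.85 = 32.0%.
- Patients per arm after loss: 155 × 0.95 = 147.25, taken as 147.
- SE = √[(0.405 × 0.595 + 0.32 × 0.68) / 147] = 0.0559.
- Power = Φ[(0.075 + 0.085) / 0.0559 - 1.645] = 88.9%.

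This agrees with 88.8%. In reverse, 147 per arm gives 294 / 0.95 = 310.

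**Step 2: precision against the margin.**
- Planning rates: half-width 1.645 × 5.59 = 9.2 points.
- Equal rates of 40.5%: SE = √(2 × 0.405 × 0.595 / 147) = 5.73 points and half-width 9.4 points. Power = Φ(0.075 / 0.0573 - 1.645) = about 37%.

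**Step 3: ceiling on the gain from center.** Simulated center intercepts around a 36% risk, with logit SD 0.3, 0.5 and 0.7 (assumed), give between-center shares of outcome variance of 2.0%, 5.2% and 9.5%. Scaling the SE by √(1 - share) gives power of 89.4%, 90.3% and 91.4%. This scaling ignores the cost of estimating up to 20 center effects with about 15 patients each, so it is an upper bound.

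**Step 4: simulation that includes that cost.** 294 patients, 20 centers of unequal size, 4,000 runs per case, unadjusted difference against one adjusted with fixed center effects and a binary covariate standing for access route. Simulation error is about 0.5 point.

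| Assumed center SD (logit) | Assumed covariate odds ratio | Power unadjusted | Power adjusted |
|---|---|---|---|
| 0 | 1 | 89.9% | 89.3% |
| 0.3 | 1 | 89.3% | 89.1% |
| 0.5 | 1 | 89.2% | 89.2% |
| 0.7 | 1 | 89.5% | 90.5% |
| 0.3 | 2 | 89.1% | 89.5% |
| 0.5 | 2 | 89.5% | 90.2% |
| 0.5 | 3 | 89.0% | 90.9% |

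The rows without a covariate effect change by -0.7 to +1.0 point. With a strong covariate the gain reaches about 2 points. A second simulation of center-blocked randomization gave -0.3 to +1.2 points for center and about +2 to +3 for a strong baseline covariate.

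**Step 5: validity of the unadjusted limit.** In the second simulation the true SD of the difference was 5.3 to 5.5 points, against a mean unstratified SE of 5.6 to 5.7. In the first, the unadjusted type I error with the true difference at the margin was 4.8% to 5.3%. The limit is slightly conservative and does not favour a false claim.

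**Step 6: equal true rates.** With both arms at 40.5%, power moved from 37.1% to 36.9% (center SD 0.3) and from 38.6% to 39.9% (center SD 0.5, covariate odds ratio 2). Adjustment makes almost no difference there.

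**The case against.** The strongest reply is that the article is a condensed account and a separate analysis plan, not shown, may stratify or adjust. That stands in part. The article never says that the analysis will be unadjusted, and stratification of a log-rank test or Cox model is often left to an analysis plan. For the primary endpoint, however, the article already fixes the estimator, its variance and the decision rule, and together these describe an unstratified difference. An analysis plan that added strata would be changing that published method. The point can therefore be raised, but as an improvement.

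A second reply is that the gain is negligible and there is no harm to validity. This largely stands, and it limits the weight of the point.

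Two stronger readings are tempting, and the documents support neither:
- **That the test is underpowered.** At the planning rates the stated 88.8% reproduces. The figure near 37% arises only if the assumed mortality benefit is absent. That is a separate question about the planning assumptions, and adjustment does not settle it. A half-width above 7.5 points does not by itself prevent success, because the planned difference is -8.5 points.
- **That the plan contradicts its own remark on access route.** The background section says of a cited study: "The access approach used was not included in their risk model, an important omission given the known differences in risk profiles". That study was a non-randomized retrospective analysis, where the omission risks confounding. Randomization deals with that here. The remark suggests that access route is prognostic, but not that leaving it out is inconsistent. The route is left to the operating team and may be settled after randomization, so the route actually used is not clearly a baseline covariate.

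**Conclusion.** The mismatch between design and analysis is real and its consequence is small. Leaving center out makes the one-sided limit at most slightly conservative and leaves type I error near 5%. Accounting for center changes power by about -1 to +1 point, and adding strong baseline prognostic factors gains about 2 to 3 points. These sizes rest on assumed center effects (logit SD 0.3 to 0.7) and assumed covariate strength, since the documents give neither, and on 1:1 allocation with independent death and hospitalization. The simulations did not test random center effects or a specific set of clinical covariates. The point merits a low-priority recommendation.

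**What to change.** Prespecify the primary 12-month risk difference (test minus control) in one of two forms:
- standardization from a survival model that handles censoring, with treatment, center and a short fixed list of baseline factors already collected, for example LVEF from the baseline echocardiogram; or
- a center-stratified Kaplan-Meier difference, with the stratum weights stated.

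In either form, pool small centers by a rule set in advance, for example by country, because about 15 patients per center will not support separate curves. Use a robust or bootstrap one-sided 95% limit and keep the 7.5-point margin. Stratify the log-rank test and Cox model by the same pooled centers. Report the unadjusted Kaplan-Meier difference as a sensitivity analysis. Include access route only if the planned route is recorded before randomization.

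The cost is analysis-plan wording and slightly more analysis work, plus one field in the randomization portal if planned route is wanted. The downside is a possible negligible loss of precision if center turns out not to be prognostic (89.9% to 89.3% in the simulation with no center effect, close to its error). Pooling by country would recover only the between-country part of any center effect.

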**Figure 1 Fig1:**
[figure not shown]
**Flow chart.** (TAVI, transcatheter aortic valve implantation; MDT, multidisciplinary team; LAD, left anterior descending artery; Cx, circumflex artery; RCA, right coronary artery; LMS, left main stem; SVG, saphenous vein graft; PCI, percutenaous coronary intervention; BMS, bare metal stent; DES, drug eluting stent).

### Trial conduct

ACTIVATION will be conducted at up to 20 hospitals in Europe providing TAVI using the Edwards system. Trial administration and data management will be carried out by an independent clinical trial organization, the European Cardiovascular Research Center, Massy, France. The trial is registered at http://www.controlled-trials.com (ISRCTN75836930).

### Procedural details

#### Percutaneous coronary intervention

The percutaneous coronary intervention in the test arm should be performed according to current local best practice. The use of the OMEGA bare metal stent (Boston Scientific Inc, Natick, MA, USA) or PROMUS family of drug-eluting stents (DES; Boston Scientific Inc, Natick, MA, USA) is mandatory. It is strongly recommended that patients should be pre-treated with aspirin 300 mg and either clopidgrel 600 mg, prasugrel 60 mg, or ticagrelor 180 mg as per local guidelines. Patients should also receive appropriate anticoagulant therapy during the PCI. The route of access (radial or femoral), use of further interventional techniques (for example, intravascular ultrasound, rotablation, laser atherectomy *etcetera*) and PCI equipment are at the discretion of the operator. Post-procedure aspirin should be continued at a maintenance of 75 mg o.d.. Patients should receive either clopidogrel 75 mg o.d., Prasugrel 10 mg o.d. or Ticagrelor 90 mg b.d. for 30 days after PCI for BMS or 6 months for DES as per local guidelines.

#### Transcatheter aortic valve implantation

Patients should be accepted for TAVI by a multidisciplinary team including both an interventional cardiologist and a cardiothoracic surgeon. The procedure should use the balloon-expandable Edwards SAPIEN XT prosthesis (Edwards Lifesciences, Irvine, CA, USA). The choices of prosthesis size and access route (transfemoral, transapical or transaortic) are to be left to the discretion of the operating team. Equally the intraprocedural details (local versus general anesthetic, perioperative imaging *etcetera*) should proceed as per usual practice at the enrolling center. Both aspirin and clopidogrel should be continued for at least 6 months after TAVI implantation with lifelong single anti-platelet therapy thereafter.

#### Data collection and monitoring

Data will be collected at baseline from enrolled patients including demographics, past medical history, previous cardiac investigations and current medication. Patients will undergo transthoracic ± transesophageal echocardiography at baseline, post-procedure, 1 month and 12 months. Twelve-lead electrocardiograms will be obtained at the same time points, with additional traces in the test arm pre- and post-PCI and in either arm after any clinical event thought to represent myocardial infarction and before/after any subsequent revascularization procedure. In addition to routine blood tests, a full blood count will be taken pre- and post-PCI.

Prospective monitoring of adverse and clinical events starts at randomization and continues until 12 months. Patients should be followed up to hospital discharge following PCI. All MACCE will be documented by the research coordinator using the clinical event data form. The same applies for the TAVI procedure. Patients will be followed up at 30 days and 12 months for anginal burden using the Seattle Angina Questionnaire and other end-points. Mortality data will be obtained from the Office of National Statistics in England and Wales, the General Register Office in Scotland and from the appropriate authority in other countries.

All MACCE and other serious adverse events will be recorded in the electronic Case Record Form and reported to the coordinating center within 3 working days of first identification. On receipt of notification of any trial adverse or clinical event, the coordinating center will request additional details, specific to the nature of the event. These episodes will be carefully monitored by the trial coordinator and will form part of the information provided at regular intervals to the Clinical Events and Data Monitoring Committees. The study site will also notify their ethics committee and institutional clinical risk management team according to their local policy. The Clinical Events Committee will be blinded to treatment and will consider each MACCE or adverse event reported and ratify occurrence of an endpoint according to the study definitions (according to a majority).

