### Primary endpoint

The primary endpoint is a composite of mortality and rehospitalization at 12 months since randomization. Mortality is defined as death due to any cause, the exact nature and date of which will be recorded. All deaths will be considered cardiovascular-related unless there is documentation to the contrary.

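### Secondary 12-month mortality is timed from TAVI, while the primary endpoint and, on its natural reading, event monitoring run 12 months from randomization

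*Protocol article*

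**What the plan says.** All places are in the protocol article.

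- **Primary endpoint:** "The primary endpoint is a composite of mortality and rehospitalization at 12 months since randomization".
- **Secondary endpoints, item (i):** mortality at 30 days and at 12 months, both counted from TAVI. The other items with a 12-month time point (MACCE, MI, stroke, heart failure hospitalization) name no origin.
- **Randomization:** in the test arm, "All PCI patients should undergo TAVI within the 2 weeks after this 30-day post-PCI time point". The wait before PCI is left open: "The intended timeframe for PCI should be stated at randomization". No interval from randomization to TAVI is given for controls.
- **Data collection and monitoring:** "Prospective monitoring of adverse and clinical events starts at randomization and continues until 12 months". Visits are described without an origin: "Patients will be followed up at 30 days and 12 months for anginal burden using the Seattle Angina Questionnaire and other end-points". Deaths have their own source: "Mortality data will be obtained from the Office of National Statistics in England and Wales, the General Register Office in Scotland", with the corresponding authority used in other countries. No cut-off date is stated for these register data.
- **Statistical analysis:** for secondary time-to-event outcomes, "event rates at 30 and 365 days will be calculated using the Kaplan-Meier method", followed by log rank tests and Cox models. The origin of the 365 days is not stated.

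**The concern.** Two clocks are in use for 12-month outcomes, and the treatment schedule forces them apart by at least 30 days in one randomized arm. A site that closes event collection 12 months after randomization stops before any test-arm patient treated on schedule reaches 12 months after TAVI. How far controls fall short depends on a wait that is not given, so the two arms may be followed for different lengths of time on the post-TAVI clock.

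If mortality data were also cut at that point, no such test-arm patient would be at risk at day 365 after TAVI, and a 365-day estimate on that clock would have no support in that arm. A clock that starts at TAVI also leaves out, on its literal wording, deaths during the wait for TAVI, and that wait has a scheduled minimum only in the test arm.

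**Working it through.** **1. The plan's own figure.** The only related figure is the power for the primary endpoint. It was reproduced to see whether the timing question touches it.

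- Inputs from Sample size determination: 12-month mortality 30% (control) and 20% (test), rehospitalization 15% in both arms, margin 7.5%, 310 patients, 5% loss. From Statistical analysis: one-sided 95% limit.
- Assumptions: 1:1 allocation; death and rehospitalization independent.
- Composite rates: control 1 − 0.70 × 0.85 = 0.405; test 1 − 0.80 × 0.85 = 0.320.
- Evaluable per arm: 155 × 0.95 = 147.25.
- SE = √[(0.405 × 0.595 + 0.320 × 0.680)/147.25] = 0.0558.
- Power = Φ[(0.075 + 0.085)/0.0558 − 1.645] = 88.9%, against the stated 88.8%.

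The figure reproduces. No input depends on the date of TAVI.

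**2. Monitored days after TAVI in the test arm.** Take 12 months as 365 days, and take the monitoring window to close 365 days after randomization.

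Days after TAVI = 365 − (randomization to PCI) − (PCI to TAVI)

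PCI to TAVI is 30 to 44 days by the Randomization section. Randomization to PCI is not given, so a range is assumed:

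| Assumed wait for PCI | Monitored days after TAVI | Shortfall against 365 | Monitoring needed, days from randomization |
|---|---|---|---|
| 0 days | 321–335 | 30–44 | 395–409 |
| 30 days | 291–305 | 60–74 | 425–439 |
| 90 days | 231–245 | 120–134 | 485–499 |

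The first row is the best case for a patient treated on schedule: 30/365 = 8.2% to 44/365 = 12.1% of the post-TAVI year lies outside the window.

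**3. Control arm.** The same formula gives 365 minus the wait from randomization to TAVI. That wait is not stated, so the difference between arms cannot be calculated. A control is monitored for a full 365 days after TAVI only if TAVI takes place on the day of randomization.

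**4. The 30-day time point.** Even the longest delay in the table leaves 231 monitored days after TAVI, so 30-day post-TAVI mortality is covered.

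**The case against.** **Deaths do not depend on the monitoring window.** The only 12-month endpoint labelled post-TAVI is mortality, and deaths come from national registers with no stated end date. This stands. A reader might infer that the endpoint cannot be observed in the test arm. The article does not support that, because vital status at TAVI plus 365 days is obtainable in both arms. What remains is that no section commits the trial to drawing it that far.

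**The end of monitoring is inferred.** The monitoring sentence ties only its start to randomization. The Randomization section says "Once the patient is randomized s/he will be monitored for the duration of the follow-up irrespective of subsequent clinical management" without giving a length, and the echocardiography schedule can be read as counting from the procedure. This stands in part. Randomization is the only origin that the monitoring sentence names, and it matches the primary endpoint, so it is the natural reading. If another origin was meant, the text still needs to say so.

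**The 365-day analysis has no stated origin.** This stands. The outcomes that need active monitoring may run from randomization, where the window fits exactly. An undefined 365-day post-TAVI estimate is a possibility under one reading, not something that the article plans.

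**Bias towards PCI.** A reader might infer that a shorter test-arm window flatters PCI. The article does not show this. The control wait is unknown, both arms may fall short, and Kaplan-Meier, log rank and Cox methods allow for administrative censoring. Bias of that kind would need a test-arm estimate carried forward to day 365 and set against a fuller control estimate, and no section plans that.

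**Size of the loss.** With a constant hazard at the assumed 20% to 30% annual mortality, the last 30 to 44 days of the year hold about 1.5 to 3.1 percentage points of mortality. It is tempting to quote this as the loss. It assumes that no death is captured after monitoring ends, contrary to the register sentence, and it ignores early procedural risk: the article cites 10.0% in-hospital mortality in registry patients with coronary disease. With register deaths drawn far enough, the loss is about zero.

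**Conclusion.** The time origins conflict and should be reconciled. If event monitoring closes 12 months after randomization, it covers at most 321 to 335 days after TAVI in a test-arm patient treated on schedule, a shortfall of at least 30 to 44 days that grows with any wait for PCI. This rests on the natural reading of the monitoring sentence and on the article's own PCI-to-TAVI schedule.

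The control-arm shortfall is unknown. The mortality endpoint is inconsistent with the monitoring window but remains obtainable from registers, and neither a direction nor a size of bias is established. One of 18 listed secondary endpoints is directly affected; the primary endpoint, its margin and its power are not. The point is worth acting on because randomization as the origin gives both arms the same follow-up despite the scheduled test-arm delay, and counts deaths that occur before TAVI.

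**What to change.** 1. In Secondary endpoints, item (i), time the 12-month mortality comparison from randomization. The 30-day post-TAVI figure can stay as it is.
2. State the same origin for the other 12-month and 365-day outcomes in Secondary endpoints, Data collection and monitoring, and Statistical analysis.
3. If a 12-month post-TAVI mortality figure is kept, state that vital status will be drawn from the registers to the TAVI date plus 365 days in both arms, and label the figure descriptive.

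The cost is one changed endpoint line and a few words on origin elsewhere, with no extra visits. The optional register figure is a later data draw from sources already named. The alternative of keeping the post-TAVI clock and extending monitoring would need follow-up to at least day 395 to 409 from randomization in the test arm. That costs more and would still leave the arms with unequal follow-up from randomization unless both were extended alike. As the trial is already recruiting, the change should be recorded before outcomes are compared by arm.
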